## Abstract

**Background:**

The design of personal protective equipment (PPE) may affect well-being and clinical work. PPE as an integrated item may improve usability and increase adherence by healthcare professionals. Human factors design and safety may reduce occupational-acquired diseases. As an integrated PPE, a lightweight protective air-purifying respirator (L-PAPR) could be used during health procedures where healthcare professionals are exposed to airborne pathogens. The human factors affecting the implementation of alternative PPE such as L-PAPR have not been thoroughly studied. The population of interest is health care professionals, the intervention is the performance by PPE during tasks across the three PPE types 1.) N95 respirators and face shields, 2.)traditional powered air-purifying respirator(PAPR), and 3.) L-PAPR. The outcomes are user error, communications, safety, and end-user preferences.

**Objective:**

This study will assess whether the L-PAPR improves health care professionals’ comfort in terms of perceived workload and physical and psychological burden during direct patient care when compared with the traditional PAPR or N95 and face shield. This study also aims to evaluate human factors during the comparison of the use of L-PAPR with a combination of N95 respirators plus face shields or the traditional PAPRs.

**Methods:**

This is an interventional randomized crossover quality improvement feasibility study consisting of a 3-site simulation phase with 10 participants per site and subsequent field testing in 2 sites with 30 participants at each site. The 3 types of respiratory PPE will be compared across medical tasks and while donning and doffing. We will evaluate the user’s perceived workload, usability, usage errors, and heart rate. We will conduct semistructured interviews to identify barriers and enablers to implementation across each PPE type over a single continuous wear episode and observe interpersonal communications across conditions and PPE types.

**Results:**

We expect the research may highlight communication challenges and differences in usability and convenience across PPE types along with error frequency during PPE use across PPE types, tasks, and time.

**Conclusions:**

The design of PPE may affect overall well-being and hinder or facilitate clinical work. Combining 2 pieces of PPE into a single integrated item may improve usability and reduce occupational-acquired diseases. The human factors affecting the implementation of an alternative PPE such as L-PAPR or PAPR have not been thoroughly studied.

**International Registered Report Identifier (IRRID):**

PRR1-10.2196/36549

## Introduction

### Background

This study aims to evaluate human factors during the comparison of the use of lightweight protective air-purifying respirator (L-PAPR) with a combination of N95 respirators plus face shields or the traditional powered air-purifying respirators (PAPRs). Health care professionals include medical doctors, nurses, respiratory therapists, physical therapists, and occupational therapists. The rationale for this research is to evaluate human factor–friendly options for hospitals facing a shortage of disposable N95 respirators or other respirators approved by the National Institute for Occupational Safety and Health (NIOSH). We evaluate the use of PAPRs to protect health care professionals against exposure to aerosols containing the coronavirus SARS-CoV-2 during direct patient care. In these situations, the design of personal protective equipment (PPE) may impact overall well-being and the PAPR design may hinder or facilitate clinical work [1]. The use of PAPRs is an alternative to conventional PPE and is currently used for the care of patients with Ebola and SARS-CoV-2 [2,3]. During the tragic 2014-2016 Ebola outbreak in West Africa, in which many health care workers died, health care professionals commonly used 10 or more distinct and disparate pieces of PPE to protect themselves. Simple protocols to correctly and comfortably don or apply PPE (donning) and remove or doff PPE (doffing) can save lives by reducing infection [2,3]. In Ebola, fear led to donning and doffing protocols that were cognitively burdensome and presented a safety risk [4]. The need to integrate PPE is a necessary design challenge to render it simple, safe, and user-friendly [5]. The use of a face shield in PPE combined with respirators can limit the visualization of facial expressions as they are obscured by the respirator [6]. In these situations, the PPE design can impact professional morale and present an obstacle to clinical care. During the COVID-19 pandemic, health professionals reported discomfort after wearing N95 respirators and eye protection (goggles or face shields) for extended shifts [7]. In addition, N95 respirators were in short supply worldwide during the pandemic, which required taking unusual decontamination measures so that they could be reused; however, decontamination does not clean PPE and led to concerns of wearing stained and unclean PPE [7]. The use of reusable PAPRs may offer improved usability, patient interaction leading to more humane clinical care, and reusability and sustainability, limited only by the maximum number of disinfection cycles before filters degrade.

The L-PAPR is an integrated PPE that may confer safety and comfort advantages to workers, which a clinician can don and doff without an assistant, unlike the traditional PAPR where assistance is needed to don and doff safely. The L-PAPR may reduce the respirator supply challenges as it is designed for multiple years of use rather than a single use only and this may in turn reduce solid waste production. Combining 2 pieces of PPE into a single integrated item may improve usability and comfort, increasing the adherence to an adequate use of PPE, and thus minimizing the risk of occupational-acquired diseases. Studying the human factors that can affect the use and implementation of alternative PPE could support the decision-making process when defining PPE usability for health care settings during the COVID-19 pandemic and in ongoing or future infectious disease outbreaks worldwide.

The PAPR is an air-purifying respirator that uses a blower to force air through the filter cartridges into the user’s breathing zone (Figure 1B). The process creates a flow of air within the faceplate and hood or helmet, providing a higher assigned protection factor than the reusable elastomeric air-purifying faceplate (half mask) or N95 respirators [8]. A PAPR could be used during health procedures in which the health care professional is exposed to aerosol pathogens to reduce acute respiratory infections [8]. PAPRs can reduce the user-inhaled aerosol concentration to at least one-quarter of that in air, compared with a one-tenth reduction for N95 respirators. This is largely due to its perfect fit to the user’ face, which reduces the inhalation of unfiltered ambient air. Traditional PAPRs have ventilation systems attached and connected to a filtered air supply mechanism. L-PAPRs are battery-operated ventilation systems that allow independent ventilation and air filtration without the encumbrance of the hose. The models we will use for this study are the Versaflo (PAPR A; 3M) [9] and the TIKI Medical Respirator (L-PAPR B; Figure 1A,B) [10].

**Figure 1 figure1:**
[figure not shown]
(A) Traditional powered air-purifying respirator (PAPR) and (B) lightweight protective air-purifying respirator (L-PAPR).

A previous study demonstrated that PAPRs mitigate the hemodynamic brain effects induced by the prolonged use of N95 respirators during 12- and 24-hour shifts [7]. In another study, health care professionals indicated a preference for PAPRs over N95 respirators in high-risk settings compared with “usual circumstances,” citing comfort, ease of communication, and an enhanced sense of personal safety [3]. A systematic review identified no difference in the contamination of health care professionals by comparing a PAPR with other respiratory protection equipment; additionally, the PAPR was identified as providing greater heat tolerance despite decreased mobility and auditory function [8].

This study aims to evaluate human factors during the comparison of the use of a lightweight PAPR with a combination of N95 respirators plus face shield or traditional PAPR to provide data on usability, design, and implementation for future work. We propose to measure the perceived workload during clinical tasks while using 3 combinations of PPE, first in a simulation project with 3 sites (Stanford, CA, USA; Bologna, Italy; and São Paulo, Brazil), followed by on-site implementation in places of care—COVID-19 wards and the intensive care unit (ICU) at 3 clinical sites (1 in Bologna and 2 in São Paulo, where health care for severe COVID-19 is provided).

### Objectives

The specific objectives of this study are follows:

To measure the perceived workload of 3 PPE combinations and to evaluate and compare across objectives 2-4.To measure human errors, equipment failure, and human factors across each of the 3 PPE conditions over a single continuous wear episode.To observe the effects of PPE on interpersonal communications.To evaluate parameters related to stress across PPE conditions and tasks to evaluate the usability perception of health care professionals about the 3 PPE conditions.

## Methods

### Study Design

This is an interventional crossover human factors feasibility study combining a simulation study (phase 1) performed in 3 sites (Stanford, Bologna, and São Paulo). Field testing (phase 2) will be performed in 2 sites (Bologna and São Paulo) across 3 ICUs. The results from phase 1 will be integrated with a collaborative study conducted at Stanford (CA, USA). The study design and phases of the research are summarized in Figure 2.

**Figure 2 figure2:**
[figure not shown]
Phases of the study design and sites where the protocol will be put into action. L-PAPR: lightweight protective air-purifying respirator; PAPR: powered air-purifying respirator.

### Inclusion and Exclusion Criteria

See Textbox 1 for details.

A limited number of participants who join the simulation in phase 1 may also volunteer to participate in the field observation phase of the study to provide observations for error similarity between field and simulation sites. Participants who withdraw from the study for any reason after initial consent will be excluded from the analysis.

This research is a 2-phase project consisting of a simulation phase and a field test phase. The results from the simulation phase will be augmented with a parallel study performed at Stanford, where visual and auditory testing will be provided. Stanford will also use part-task trainers as well as high-fidelity complex simulations. During the simulation phase, the Stanford site will test multiple intubation methods. Training with complex and part-task trainer simulations allows testing of the fidelity of part-task trainers. Their lower cost may make them a more viable option in lower-resource settings [11].

This assessment of PPE evaluates human factors in the relationship between PPE (technology) and the clinician (end user). It is hoped that insights from this research might be used to tailor the design of PPE technology for mucosal protection in situations such as admissions, emergency department and ICU care, and in triage centers, where first responders deliver the patient for emergency medical services. According to the Clinical Human Factors Group, “Human factors are organizational, individual, environmental, and job characteristics that influence behavior in ways that can impact safety” [12].

Inclusion and exclusion criteria.

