**Exclusion criteria**
Minors, health care professionals under 18 years of age.Nonhospital site employees.Clinicians without experience of caring for patients with COVID-19.COVID-19 exposure.Positive prestudy screening for COVID-19, including respiratory symptoms or fever.Participants who fail the NIOSH fit test for the L-PAPR.Any individual for whom simulation is contraindicated.

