### Randomization

Participants will be recruited among health care professionals employed in field settings. Participants will be computer randomized and assigned to 1 of 3 PPE conditions on the day of the study and randomization will occur before study and between conditions. The Stanford simulation site will compare the 3 PPE types, namely, A (L-PAPR), B (respirator and face shield), and C (traditional PAPR). São Paulo and Bologna sites will have 1 intervention arm, A (L-PAPR), and 1 comparator arm, B (respirator and face shield, São Paulo) or C (traditional PAPR, Bologna). The randomizing sequence for each site will be AB or BA (São Paulo) and AC or CA (Bologna). A minimum of 10 participants will be recruited in each simulation site. As this is a crossover design, participants will be assigned to the intervention and comparator arms, and they will be randomized to the use of equipment to reduce order effects, a well-documented phenomenon that suggests different orders or times in which the interventions are presented can influence outcomes.

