### Consent

Participants will sign an informed consent form in their native language. The risk to participants is less than what they encounter in a clinical workday. Before signing, the participants who gave consent will receive detailed information on the types of PPE and monitoring devices to be used, including photographs, infographics, and instructional videos to facilitate their understanding of the methods to be employed. The participants will be informed that they can withdraw at any time of the study. Each participant will be provided with a unique code to protect their anonymity. The investigators will ensure participants understand the implications of their involvement (risk and benefits), their right to withdraw, that their participation is voluntary, and how information collected during the study will be used and reported. Participants’ comprehension of the materials will be tested using teach-back methods and a questionnaire. The informed consent script “Verbal Consent Script to Inform Participants in a Research Study: Field Observations” will be used to guide this discussion and versions for each country can be accessed from Multimedia Appendix 1.

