### Phase 2: Field Testing

#### Steps Overview

Phase 2 field testing will follow simulation testing so that early observations can be applied, and conditions adapted to improve field testing. Over a single shift of direct patient care, the following tasks will be performed, and they will be timed per task and participant. Our hope is that timing the tasks will contribute to assessing how errors occur; for example, we will report whether errors are task related, whether tasks with longer run times produce increased errors, or if errors occur early in the process and become less likely as health care professionals become accustomed to using PPE or performing specific tasks.

#### Step 1

Participants will be supplied with smartwatches, which will allow their movement (eg, number of steps) and HR to be recorded and automatically uploaded to the smartphone software before being recorded on the smartwatch company servers.

#### Step 2

Health care professionals will don the PPE to which they are randomized. Researchers will observe the health care professionals using each PPE combination and will record the instances of PPE readjustments (eg, repositioning of the mask) and user or equipment errors. If the health care professional removes the PPE combination for reasons unrelated to the clinical task, this event and the time of occurrence will be recorded.

#### Step 3

Following the simulation shift, researchers will administer the NASA-TLX questionnaire [17] and the SUS questionnaire [18]. Following this, the researchers will conduct a 15-20-minute semistructured interview to elicit human factors related to the success and failure of PPE implementation. For those seeking more details for conducting all steps including time recording per task, see Multimedia Appendix 1. Table 1 is an approximation of time for tasks, and this was piloted across the sites.

**Table 1 table1:** Tasks time; comparator and intervention simulation will be randomized.

Start	Stop	Time	Description
		0:15	Sign consent forms and study check-ins
		0:05	Donning Change into PPE^a^ and smartwatch function check
		0:15	Acclimation period Take baseline vitals
		0:20	Stanford only, visual and auditory testing
		0:35	Medical Task Series
		0:05	Doffing
		0:20	Take vitals Survey (NASA-TLX^b^ and SUS^c^)
		0:20	Qualitative interview
		0:05	Debriefing and checkout
		1:40	Time per PPE session

^a^PPE: personal protective equipment.

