### Data Management and Governance

Questionnaires are hosted in the REDCap software [29]. We will compare NASA-TLX scores [17] and physiological parameters between the intervention and comparator arms. We will collect HR and the number of steps as an indirect indicator for physical activity and stress over time. Qualitative data will be transcribed verbatim and analyzed as per their content according to Krippendorf [32], identifying themes and categories that emerged from the participants’ answers. Quantitative data will analyze differences in the NASA-TLX scores between the intervention and comparator arms. There is a multisite data management and security plan in place agreed upon by the WHO and individual institutional IRBs. Identifiable data will be replaced with numeric coded identifiers. The codes used for participants in phase 1 and phase 2 will aid anonymity. Only research staff, PI, and co-PIs will know who has declined or withdrawn from the study. The identity of participants or those who decline or withdraw will not be shared outside of the local research group. Data will be stored and kept secure in accordance with IRB agreements and country legislation.

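### Dropping everyone who withdraws for any reason discards completed crossover periods and device-driven stopping, and shifts the PPE comparison if withdrawal depends on the device

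*Protocol article*

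**What the plan says.** Under Inclusion and Exclusion Criteria the protocol article gives a flat analysis rule: "Participants who withdraw from the study for any reason after initial consent will be excluded from the analysis". It makes no exception for data already collected or for stopping caused by the equipment, and no other section softens it. The Consent section adds: "The participants will be informed that they can withdraw at any time of the study". Withdrawal during a wear episode or between periods is therefore possible.

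The second objective reads: "To measure human errors, equipment failure, and human factors across each of the 3 PPE conditions over a single continuous wear episode". The Randomization section sets two-period sequences in São Paulo (L-PAPR with respirator plus face shield) and Bologna (L-PAPR with traditional PAPR), and three conditions at Stanford. The Data Management and Governance section states the main comparison: "Quantitative data will analyze differences in the NASA-TLX scores between the intervention and comparator arms".

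Two other provisions matter. In field testing (Step 2), readjustments and user or equipment errors are recorded, and if a professional "removes the PPE combination for reasons unrelated to the clinical task, this event and the time of occurrence will be recorded". The exclusion list also contains "Participants who fail the NIOSH fit test for the L-PAPR", with no matching criterion listed for the two comparators.

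**The concern.** The study asks how well each PPE type is tolerated and what would hinder its use. A participant who leaves because a respirator is uncomfortable, noisy or failing gives direct evidence on that question, and the rule takes that person out of the analysis. Such withdrawal happens after randomisation and can be caused by the condition being worn, so those who remain may be a selected group.

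The crossover adds a second cost. Someone who completes the first condition and withdraws during the second loses both, including questionnaires already answered. Table 1 places the NASA-TLX, SUS and interview inside each PPE session, so a finished first session would already have produced scores.

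The risk is plausible on the document's own evidence. The Results section mentions trouble communicating, blower noise and discomfort at the face with the light PAPRs, and the Discussion lists physical complaints from extended N95 wear. Any of the devices could prompt someone to stop.

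**Working it through.** **Inputs from the protocol article.** At least 10 participants per simulation site (Randomization) and 30 per field site (Sample Size Justification). NASA-TLX runs from 0 to 100, with higher meaning more workload (Outcome Measures).

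**Inputs not in the document, so assumed.** NASA-TLX SD σ of 15 or 20, within-person correlation ρ of 0.3 or 0.6, withdrawal proportion w of 5%, 10% or 20%, and a true difference between devices of zero. The plan has no figure of its own to reproduce.

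**Step 1: what the rule removes.** Take a participant in sequence AB.
- Completes A, starts B, takes B off and withdraws: the A scores, the A errors, the B errors and the B removal record all leave the analysis.
- Completes A, takes B off early but stays enrolled: everything is kept, including the removal and its time.

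The loss therefore arises at study withdrawal, not at PPE removal.

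**Step 2: how many are lost.** The expected loss is n × w, and the chance of losing at least one is 1 − (1 − w)^n. At w = 10%:
- n = 10: 1 expected; 1 − 0.9^10 = 65%.
- n = 30: 3 expected; 1 − 0.9^30 = 96%.

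**Step 3: shift if withdrawal is wholly driven by device A.** Let scores on A and B be normal with equal means, and let the share w with the highest workload on A withdraw and lose both periods. The completers' mean A − B difference is then −(1 − ρ) × σ × φ(z)/(1 − w), where z is the (1 − w) normal quantile and φ the normal density.

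| w | φ(z)/(1 − w) | Smallest shift (ρ = 0.6, σ = 15) | Largest shift (ρ = 0.3, σ = 20) |
|---|---|---|---|
| 5% | 0.1031/0.95 = 0.109 | 0.4 × 15 × 0.109 = 0.7 | 0.7 × 20 × 0.109 = 1.5 |
| 10% | 0.1755/0.90 = 0.195 | 0.4 × 15 × 0.195 = 1.2 | 0.7 × 20 × 0.195 = 2.7 |
| 20% | 0.2800/0.80 = 0.350 | 0.4 × 15 × 0.350 = 2.1 | 0.7 × 20 × 0.350 = 4.9 |

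All shifts favour A, the device that drove people out. A simulation with 2,000,000 draws per setting gave the same ranges.

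**Step 4: weaker mechanisms.** If half the withdrawals are driven by A and half are random, the simulated shift runs from about 0.4 points (5% withdrawal) to 2.7 points (20%). If withdrawal is random, or driven equally by both devices, it is 0.0.

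The same mechanism applies to SUS and to errors, but nothing in the document allows a size to be put on those.

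**The case against.** The strongest reply is that taking a respirator off is not withdrawing from the study. Step 2 of field testing treats removal as a recorded event, and the Outcome Measures count adjustments, errors and equipment breakdowns in both phases. This stands. A reader might infer that the rule strips device failures out of the study altogether. The documents do not support that, because the loss is confined to people who leave the study.

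A reader might also infer that the results are biased, and biased towards the L-PAPR. Neither follows. No withdrawal rate or reasons are given, the shift is zero under unrelated or balanced withdrawal, and its direction depends on which device people leave. Nor is the change in one device's own mean the right measure. Dropping both periods also removes the quitter's comparator score, so the within-person difference moves less.

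The fit-test criterion is a different matter from the withdrawal rule. It is an eligibility condition applied before the study, in staff who may work in COVID-19 areas. Everyone analysed has passed it, so it does not by itself bias their within-person comparison. It only narrows the population to which the results apply. Nor does the article say that screening failures will go unreported.

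Finally, this is a feasibility study that disclaims power. That lowers the stakes for inference, but it does not excuse the rule. Arms are still to be compared on NASA-TLX, and in a feasibility study the number who stop with each device is one of the more useful results.

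**Conclusion.** The withdrawal rule is a stated analysis choice that does not suit this study, and it should be replaced. It discards completed periods with certainty whenever someone withdraws after the first condition, and it hides device-driven stopping whenever that occurs. Any shift in the scores is conditional. With wholly device-driven withdrawal it is about 1.2 to 2.7 NASA-TLX points at 10% and 2.1 to 4.9 points at 20%, and it falls to zero when withdrawal is unrelated to device or balanced. These figures rest on the assumed SDs, correlations and withdrawal rates and on the worst-scoring participants being the ones who leave. They show scale and do not predict a result. With withdrawers left out of the analysis, a reader could not judge from it which case applied.

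The fit-test exclusion is a secondary matter of generalisability and reporting.

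**What to change.** Replace the sentence with wording such as: All randomised participants are analysed with all data collected up to withdrawal, unless the participant withdraws permission to use the data. Withdrawals are reported by PPE condition, period, reason and time as a usability outcome. NASA-TLX and SUS are requested at the point of stopping where the participant agrees.

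Report the number fit-tested for the L-PAPR and the number failing. No change to the eligibility or fit-test rule is proposed.

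The cost is one paragraph. Removal events and times are already collected in the field phase. The Results section reports 80 participants already recruited in Bologna and São Paulo; for anyone among them who has already withdrawn, only data in hand can be kept, subject to their consent. The confidentiality provisions protect identities, so aggregate counts remain reportable, pooled over sites where cells are very small.

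The downside is some incomplete pairs. Because dropout may be informative, the withdrawal counts must be read beside the scores, and a model should not be relied on to correct for it.
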